## 1. INTRODUCTION AND RATIONALE

Cardiovascular disease (CVD) is the leading cause of death in patients with end-stage renal disease (ESRD). From several perspectives, the pathophysiology of ischemic cardiovascular events is different in ESRD compared to the general population. In patients with ESRD, the classical risk factors for CVD, such as hypertension, obesity and hyperlipidemia are associated with decreased mortality instead of increased mortality ("reverse epidemiology"). Vascular calcification appears to be the central finding in the pathophysiology of CVD, manifesting itself in increased arterial stiffness and mediasclerosis. The presence and extent of vascular calcifications are strong predictors of all-cause and cardiovascular mortality in hemodialysis patients, independent of classical atherogenic factors.

Elevated calcium and phosphate concentrations or loads in the serum of ESRD patients have direct effects on vascular smooth muscle cells that induce an osteogenic "bone-like" differentiation of these cells. Reducing the calcium concentration in ESRD patients by the prescription of non-calcium-containing phosphate binders can slow down the progression rate of arterial calcification. Coronary artery calcification in young hemodialysis patients is strongly associated with dialysis vintage, calcium-phosphorus-product and oral calcium load.

It has been well documented that correction of calcium and phosphorus parameters is also possible by means of long and frequent hemodialysis, such as nocturnal hemodialysis. A single short-term study on nocturnal hemodialysis showed stabilization of coronary artery calcification score, but comparison with renal transplantation and conventional hemodialysis and peritoneal dialysis was not made. Therefore this study aims to compare the progression of coronary artery calcification score in 4 models of treatment of ESRD: conventional hemodialysis, peritoneal dialysis, renal transplantation and nocturnal hemodialysis.

A second question that is unanswered so far, is the pathophysiology of the vascular calcification in ESRD patients. In ESRD, serum is oversaturated with calcium and phosphorus, and in vitro precipitation would occur with the present calcium and phosphorus concentrations. Extracellular calcium-regulatory proteins, such as matrix gla protein (MGP), osteoprotegerin and human fetuin-A, are potent inhibitors of calcium-phosphorus precipitation. Animals lacking these proteins die at young age due to arterial calcifications and vessel ruptures. The serum concentration of fetuin-A is diminished in ESRD, and rises after a renal transplant. Fetuin-A-deficiency is an inflammation-related mortality risk factor and the possible missing link between chronic inflammation and high incidence of cardiovascular events in dialysis patients. However, contradictory reports describe the course of fetuin-A deficiency in renal insufficiency and diabetic nephropathy. Regarding MGP, an inverse relation between undercarboxylated MGP and aortic augmentation index, a marker of vascular stiffness, was found, suggesting that low MGP levels are a marker of active calcification.

Therefore this study aims to study non-classical risk factors in patients with ESRD, such as the calcium-regulatory proteins and inflammatory parameters. We expect that patients with advanced age, long period on dialysis, a high calcium phosphate product, increased inflammation markers and deficiency of calcification inhibitors will show the highest progression of coronary calcification. How these factors interact with the treatment modalities under study, remains to be established.

The primary endpoint of this study is the change in coronary calcification score, visualized by multi-slice CT scanning. With this technique, the amount of calcification in coronary arteries can be quantified during 3 heartbeats (i.e. in about 10 seconds) with radiation exposure less than a conventional CT-scan. The burden of this technique is therefore minimal for the patient.

## **2. OBJECTIVES**

### **Primary objective:**

1. To assess whether frequent nocturnal hemodialysis and renal transplantation are associated with less progression of coronary artery calcifications, in comparison with conventional 3-times/week hemodialysis and with peritoneal dialysis.

### **Secondary objectives:**

1. To assess whether frequent nocturnal hemodialysis and renal transplantation are associated with less progression of coronary artery stenoses, in comparison with conventional 3-times/week hemodialysis and with peritoneal dialysis;
2. To assess the association of calcium-homeostasis, in particular calcium, phosphate, PTH, and relevant medication, with the progression of coronary arterial calcifications and stenoses;
3. To assess the association of markers of inflammation, in particular CRP, interleukin-6, interleukin-1, von Willebrand factor, fibrinogen, with the progression of coronary arterial calcifications and stenoses;
4. To assess the association of calcification-inhibitors, in particular fetuin A, osteoprotegerin and matrix-Gla protein, with the progression of coronary arterial calcifications and stenoses.
5. To assess possible interaction of the abovementioned risk factors and the treatment modalities mentioned in the primary objective.

### 3. STUDY DESIGN

The study is a prospective cohort study, with a duration of follow-up of 3 years. The design is schematically depicted in the following flow charts.

[figure not shown]

#### Investigations:

| time                                | incl | ½ yr | 1 yr | 1 ½ yr | 2 yr | 2 ½ yr | 3 yr |
|-------------------------------------|------|------|------|--------|------|--------|------|
| Multi-slice CT scan (MSCT) of heart | x    |      | x    |        | x    |        | x    |
| Coronary MSCT                       | x    |      |      |        |      |        |      |
| Pulse-wave velocity                 | x    |      | x    |        |      |        | x    |
| Lab assessments                     | x    | x    | x    |        | x    |        | x    |
| Weight/Blood pressure               | x    |      | x    | x      | x    | x      | x    |
| Medication                          | x    |      | x    |        | x    |        | x    |
| Quality-of-life                     | x    |      | x    |        | x    |        | x    |
| Karnofsky perf. status              | x    |      | x    |        | x    |        | x    |
| Clinical events                     |      |      | x    |        | x    |        | x    |
| continuously                        |      |      |      |        |      |        |      |

## **4. STUDY POPULATION**

### **4.1 Population**

The study populations consists of 4 cohorts of patients: patients who start with frequent nocturnal hemodialysis, patients who receive a renal transplant and 2 control groups treated with hemodialysis and with peritoneal dialysis. The study is sponsored by Dianet Dialysis Centers, while all research activities take place in University Medical Center Utrecht. Patients were screened at their local treatment facility (Dialysecentrum Groningen, Groningen; Dialysecentrum Diapriya, Amsterdam; VU medisch centrum, Amsterdam; Meander Medisch Centrum, Amersfoort; Rijnstate Ziekenhuis, Arnhem; Sint Antoniusziekenhuis, Nieuwegein; Stichting Dianet Dialysecentra, Utrecht and Amsterdam; and University Medical Center Utrecht, Utrecht), and if interested in the study, subsequently referred to University Medical Center Utrecht for study participation.

- 40 patients who start treatment with frequent nocturnal hemodialysis are asked to participate in the study;
  - 40 patients who receive a renal transplant, after having been treated with hemo- or peritoneal dialysis, are asked to participate in the study;
  - 40 patients who are treated with conventional hemodialysis are asked to participate; in order to enhance similarity between groups only hemodialysis patients are recruited that are or could be eligible to be on the waiting list for renal transplantation;
  - 40 patients who are treated with peritoneal dialysis are asked to participate; in order to enhance similarity between groups only peritoneal dialysis patients are recruited that are or could be eligible to be on the waiting list for renal transplantation.
- Groups will be matched according to age, sex, presence of diabetes mellitus and duration of dialysis, in order to minimize between-group differences to 25% regarding these factors.

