### **4.2 Inclusion criteria**

- current age > 18 and < 75 yr
- ability to understand the study procedures
- willingness to provide written informed consent

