### **4.3 Exclusion criteria**

- life expectancy < 3 months
- claustrophobia
- treatment incompliance, i.e. non-adherence to dialysis regimens and drug use
- GFR < 30 ml/min (according to MDRD formula) in renal transplant patients
- pregnancy

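### Waiting-list eligibility is required of the conventional hemodialysis and peritoneal dialysis groups but not of the nocturnal group, so comparability on it is not ensured in the two nocturnal contrasts of the primary objective

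*Protocol*

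**What the plan says.** Protocol section 4.1 describes the four cohorts in four bullets.

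- Conventional hemodialysis carries an eligibility condition and a reason for it: "in order to enhance similarity between groups only hemodialysis patients are recruited that are or could be eligible to be on the waiting list".
- Peritoneal dialysis carries the same condition: "only peritoneal dialysis patients are recruited that are or could be eligible to be on the waiting list for renal transplantation".
- Nocturnal hemodialysis carries none: "40 patients who start treatment with frequent nocturnal hemodialysis are asked to participate in the study".
- Transplantation needs none, since these patients are transplanted: "40 patients who receive a renal transplant, after having been treated with hemo- or peritoneal dialysis, are asked to participate in the study".

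The section then adds matching, with between-group differences to be kept within 25%: "Groups will be matched according to age, sex, presence of diabetes mellitus and duration of dialysis". Eligibility for transplantation is not one of the four factors.

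The criteria common to all cohorts do not supply the condition. Section 4.2 asks for an age range ("current age > 18 and < 75 yr"), understanding of the procedures and consent. Among the exclusions in 4.3, the one that speaks to prognosis is "life expectancy < 3 months". Neither the population list in the Summary nor the definition of nocturnal hemodialysis in 5.1 mentions eligibility.

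The primary objective in section 2 is "To assess whether frequent nocturnal hemodialysis and renal transplantation are associated with less progression of coronary artery calcifications", with conventional hemodialysis and peritoneal dialysis as comparators.

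**The concern.** Patients choose their modality, so the comparison of cohorts rests on restriction, matching and adjustment. The sponsor selected transplant eligibility as a restriction because it expected it to make the groups more alike, and then did not state it for the one dialysis modality under test. As written, a patient who could never be listed may enter the nocturnal group but neither of its two dialysis comparators.

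Eligibility plausibly reflects comorbidity and frailty, which may also relate to the progression of calcification. If the nocturnal group contains ineligible patients, nocturnal versus conventional hemodialysis and nocturnal versus peritoneal dialysis would compare groups that differ in more than modality. These two contrasts are half of the primary objective. The schedule of investigations and section 7.3 list no eligibility item, so the final report might be unable to show whether the difference exists.

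**Working it through.** **1. The condition, cohort by cohort**

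| Cohort | Eligibility condition | Source |
|---|---|---|
| Nocturnal hemodialysis | none stated | Summary, 4.1, 4.2, 4.3, 5.1 |
| Transplant | met by definition | 4.1 |
| Conventional hemodialysis | required | 4.1 |
| Peritoneal dialysis | required | 4.1 |

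**2. Contrast by contrast**

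- Nocturnal versus conventional hemodialysis, and nocturnal versus peritoneal dialysis: eligibility is fixed on one side only, so comparability is not ensured.
- Transplant versus either comparator: eligible on both sides, so the rule helps.
- Nocturnal versus transplant: the rule restricts neither group and changes nothing. This contrast appears in the Summary's hypothesis but not in the primary objective.

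**3. Does the rule widen or narrow the gap?** Let fA be the ineligible share in the nocturnal group and fC the share a comparator would have without the rule. The gap in eligibility is |fA − fC| without the rule and fA with it. The rule widens the gap only if fC < 2·fA. With assumed values:

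- fA = 25%, fC = 25%: gap 0 without the rule, 25 points with it.
- fA = 10%, fC = 50%: gap 40 points without the rule, 10 points with it.

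The Protocol gives neither share, so both cases remain open.

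**4. The plan's own yardstick.** Section 4.4 gives mean 2370, SD 352 in the text, a difference of 15% (0.15 × 2370 = 355.5), two-sided alpha 0.05, power 0.90 and 22 patients per group. The printed formula gives 2 × (1.96 + 1.28)² × 352 / 355.5 = 20.8, so 21. A t-based calculation gives 21.6, so 22. The stated figure reproduces to within one patient. Power at 22 per group is 0.92 by normal approximation.

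**5. Illustration of size, by assumption only.** Let g be the excess change in ineligible patients, in points of the mean score. The bias in a nocturnal contrast is then fA × g. The last column is the power, at 22 per group, to detect a true 15% benefit of nocturnal dialysis if the bias works against it.

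| fA | g | Bias (points) | Share of the 15% target | Power |
|---|---|---|---|---|
| 0% | any | 0 | 0 | 0.92 |
| 10% | 15 | 1.5 | 0.10 | 0.85 |
| 25% | 30 | 7.5 | 0.50 | 0.39 |
| 50% | 30 | 15 | 1.00 | no better than chance |

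Neither fA nor g has a source in the Protocol. The product also assumes that matching and adjustment remove none of the difference, so for given fA and g these are upper values.

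**6. Cost of restricting the primary contrast to eligible patients.** With 22 nocturnal completers and an assumed 20% to 50% ineligible, 0.80 × 22 = 17.6 (about 18) to 0.50 × 22 = 11 remain. Against 22 comparators, power is Φ(355.5 / [352 × √(1/22 + 1/n)] − 1.96), which is 0.89 for n = 18 and 0.78 for n = 11, compared with 0.92 for n = 22.

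**The case against.** A reader might infer that the restriction creates an imbalance in the main contrasts of the study. The Protocol does not support that.

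- **Imbalance is not shown.** Section 5.1 says nocturnal hemodialysis is mostly done at home. The Summary and sections 7.4 and 7.5 foresee transplantation in all three dialysis groups. A largely eligible nocturnal group is plausible, and the rule would then bring the comparators closer to it. This objection stands: the text permits an imbalance but does not establish one.
- **Not all contrasts are touched.** Transplant versus the two comparators benefits from the rule, and nocturnal versus transplant is unaffected by it. This stands and limits the point to two contrasts.
- **Part of any difference may be removed.** Matching covers age, sex, diabetes and dialysis duration, section 9.2 corrects for the initial score, and section 9.3 names performance status. This stands only in part. Sections 9.2 and 9.3 are written mainly for the risk-factor associations, section 9.1 says only that groups are compared by regression, and performance status is at best a proxy for eligibility.
- **The study is openly observational.** Some confounding by choice of modality is unavoidable. That is true, but this particular source was identified by the sponsor and can be measured at little cost.

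A reader might also infer that the bias could consume most of the 15% target. That needs ineligible shares and excess progression that the Protocol does not give. Zero is equally compatible with the text.

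**Conclusion.** The point holds in limited form. Section 4.1 applies its own similarity condition to the two dialysis comparators and not to the nocturnal group, and neither the matching factors nor the named covariates make up for this. Comparability on transplant eligibility is therefore not ensured for nocturnal versus conventional hemodialysis or nocturnal versus peritoneal dialysis.

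The presence and size of a bias are unknown, because the share of ineligible nocturnal patients and their excess progression are not given. The direction is also an assumption. If ineligible patients progress faster, nocturnal hemodialysis would look worse than it is, so a benefit could be masked; a spurious benefit would not arise from this source. No sample-size figure changes. This is a cheap improvement to the design, not evidence that the primary comparison is invalid.

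**What to change.** 1. Record at inclusion, for every nocturnal patient, whether the patient is or could be eligible for the waiting list, using the criterion already applied to the two comparator groups. For patients already enrolled, establish it as of their inclusion date.
2. Keep all nocturnal patients in the primary contrast and report the eligible share.
3. Add a sensitivity analysis of the two nocturnal contrasts limited to eligible patients.
4. For patients not yet recruited, apply the eligibility sentence in 4.1 to the nocturnal group as well.

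The cost is one item on the inclusion form, one protocol sentence, a sensitivity analysis less precise than the primary one, and possibly slightly slower nocturnal recruitment. Making the eligible-only comparison primary is not advised, because of the loss of power shown in step 6 of the working if many patients prove ineligible.

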### **4.2 Inclusion criteria**

- current age > 18 and < 75 yr
- ability to understand the study procedures
- willingness to provide written informed consent

### **4.3 Exclusion criteria**

- life expectancy < 3 months
- claustrophobia
- treatment incompliance, i.e. non-adherence to dialysis regimens and drug use
- GFR < 30 ml/min (according to MDRD formula) in renal transplant patients
- pregnancy

### **4.4 Sample size calculation**

The effects of the different modalities of renal replacement therapy on arterial calcification are analyzed with linear regression, after transformation of calcium scores. The effects of risk

factors for calcification, including inflammation parameters and calcification inhibitors are analyzed in a multivariate model. The mean ( $\pm$ SD) coronary calcification score in ESRD patients is 2370 ( $\pm$  352). The multislice CT-scan is extensively validated in our institute. At this level of calcification the variation between independent measurements is less than 10%. Therefore we can demonstrate an increase or decrease in calcification score of 15%, in 4 subpopulations of 22 patients with ESRD, with a type I error probability for a two sided test of 0.05 and a power of 0.90 [formula: " $N = (2(Z_{\alpha} + Z_{\beta})^2 \cdot sd) / (0.15 \cdot \text{mean})$ " where N = number of patients per group,  $Z_{\alpha} = 1.96$ ,  $Z_{\beta} = 1.28$ ,  $S = 3.52$ , mean = 2370]. To account for a dropout of patients by renal transplantation, switch to a different treatment modality, refusal of further participation or death we intend to include 40-55 patients per group – depending on the dropout, aiming to obtain complete study data in 22 patients per group.

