## **7. METHODS**

### **7.1 Study endpoints**

#### 7.1.1 Main study endpoint

The primary endpoint of the study is:

- change in coronary artery calcification score

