## **9. STATISTICAL ANALYSIS**

### **9.1 Descriptive statistics**

The population characteristics are described with a categorical or continuous output, as appropriate.

The primary endpoint, coronary artery calcification score, is a continuous variable with a skewed distribution, and will be presented with its median and ranges. Progression of calcification score will be analyzed with multinomial logistic regression, dividing the coronary artery calcification score in three categories. The same goes for pulse wave velocity of the aorta and iliac arteries.

The calcification score of the different groups will be compared by regression analyses.

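### The 90% power with 22 completers per group is derived from the spread of a single calcification score, not of change in score, so it is unsupported for the primary endpoint, in an unknown direction; the formula is also misprinted, without effect on N

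*Protocol*

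**What the plan says.** Section 4.4 takes the mean (SD) of the score from a cited study: the "coronary calcification score in ESRD patients is 2370", with SD 352. It adds that repeat measurements at this level vary by less than 10%, and then concludes: "Therefore we can demonstrate an increase or decrease in calcification score of 15%, in 4 subpopulations of 22 patients with ESRD". The test is two-sided at the 0.05 level and the claimed power is 0.90. The printed formula is N = 2(Zα + Zβ)² · sd / (0.15 · mean), with Zα = 1.96 and Zβ = 1.28. Its legend gives S as 3.52 and the mean as 2370. Recruitment of 40 to 55 per group is meant to leave 22 with complete data.

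The primary endpoint in section 7.1.1 is "change in coronary artery calcification score", and the Summary makes clear that this is per patient. The primary objective in section 2 is a comparison of progression between modalities. Section 4.4 itself plans linear regression on transformed scores. Section 9.1 says that the score "is a continuous variable with a skewed distribution, and will be presented with its median and ranges" and also plans multinomial logistic regression for progression, using three categories. Section 9.2 corrects for the initial score in its univariate regressions.

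**The concern.** A power statement holds only for the variable whose SD went into it. Here that SD describes how much ESRD patients differ from one another at one time. The study asks how much progression differs between modalities, and the relevant spread is that of change in score between patients. The two are linked through the correlation between baseline and follow-up, which the protocol does not give.

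The repeatability figure of less than 10% does not fill the gap. It describes how closely two measurements agree, not how differently patients progress. It is also not an input to the formula, although the power claim is worded as if it followed from it. Nor does the text say whether 15% is a change within a group or a difference between groups in progression.

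This paragraph is the only justification for 22 completers per group. If the modalities turn out not to differ, the result would be read against a 90% power claim that was never derived for progression.

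**Working it through.** **Inputs from section 4.4.** Mean 2370; SD 352; relative difference 15%; Zα = 1.96; Zβ = 1.28; 22 per group.

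**Step 1. Reproduce the stated figure.**
- Difference: 0.15 × 2370 = 355.5.
- Multiplier: 2 × (1.96 + 1.28)² = 2 × 3.24² = 20.995.
- Correct formula, N = 2(Zα + Zβ)² · SD² / δ²: 20.995 × (352/355.5)² = 20.6, so 21.
- Exact t-test: 22 per group is the smallest number that reaches 90%, with power 0.905 (0.891 at 21).

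The 22 therefore reproduces from the protocol's own mean and SD.

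**Step 2. The formula as printed.**
- Unsquared with SD 352: 20.995 × 352/355.5 = 20.8, so 21.
- Unsquared with the legend's 3.52: 20.995 × 3.52/355.5 = 0.21 patients.

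The value 3.52 cannot have been used. Omitting the squares is harmless here only because 352/355.5 = 0.99. That agreement disappears with another SD: at 700 the unsquared form gives 20.995 × 700/355.5 = 41.3, and the correct form gives 20.995 × (700/355.5)² = 81.4.

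**Step 3. Power for change in score.** No SD of change is given, so no single figure can be computed. Assume equal variances at both times, with ρ the baseline/follow-up correlation. Then SD of change = 352 × √(2(1 − ρ)). Take 355.5 as the between-group difference in change. Exact two-sided t power at alpha 0.05 with 22 per group:

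| Assumption | SD of change | Power |
|---|---|---|
| ρ = 0 | 498 | 0.64 |
| ρ = 0.3 | 416 | 0.79 |
| ρ = 0.5 | 352 | 0.905 |
| ρ = 0.7 | 273 | 0.99 |
| ρ = 0.9 | 157 | near 1 |
| SD of change set to 500 | 500 | 0.63 |
| SD of change set to 700 | 700 | 0.38 |

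At ρ = 0.5, √(2 × 0.5) = 1, so the SD of change equals the SD of the score. Using 352 for change therefore amounts to assuming ρ = 0.5 without saying so. These figures are on the raw scale and show only how far the answer depends on the missing quantity. They are not the power of the regression on transformed scores.

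**Step 4. Is 352 plausible beside section 9.1?** The coefficient of variation is 352/2370 = 0.149. A lognormal variable with that value has skewness 0.45 and median 2344, about 1% below the mean. Its central 95% runs from about 1755 to 3130. That is a mildly skewed, narrow distribution, and it fits poorly with a score that the protocol reports by median and range and transforms before analysis.

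**The case against.** The strongest reply is that the number stands. The correct formula with 352 gives 21 to 22, and the legend value is plainly a typing slip (a slip in reading the PDF cannot be excluded). That is right: the misprint is a reporting error and does not drive N.

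A second reply is that the substitution may be conservative. If SD 352 is right, variances are equal and the correlation exceeds 0.5, the SD of change is below 352 and power for the same difference exceeds 90%. That is also right. A reader might infer that the study is underpowered, but the documents do not support it. They give nothing to place the correlation or the SD of change, and the low figures in the table come from assumed values.

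Three further inferences should be resisted:
- **A much larger SD of the score, because it is skewed.** No figure in the protocol supports one. A variable with skewness 0.45 is still skewed, and transforming a score does not contradict quoting its mean and SD. Step 4 is a reason to check the source, not proof of error.
- **A lower alpha for the four contrasts in the primary objective.** The protocol of this observational cohort commits to no familywise error control, so splitting alpha would be a preference.
- **Too few patients enrolled.** Enrolment of 40 to 55 exceeds 22, and the Summary's 25% loss would leave 30 (0.75 × 40) to about 41 (0.75 × 55). This eases the worry about numbers, but the power claim in section 4.4 is made for 22 and remains unsupported for change.

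What survives is that the protocol makes a specific power claim for a variable that is not its endpoint. Since the claim is in the protocol, it cannot be set aside as a detail for a statistical analysis plan.

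**Conclusion.** The concern holds in this limited form. The 90% power is reproducible for a comparison of single scores with SD 352, and unsupported for change in score compared between modalities. The size of the error is undetermined. On the raw scale, with SD 352, equal variances and a difference of 355.5, power at 22 per group runs from 0.64 (ρ = 0) to near 1 (ρ = 0.9). It is 0.63 or 0.38 if the SD of change is 500 or 700. All these correlations and SDs of change are assumptions.

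The formula and its legend are wrong as printed, with no effect on N. The value 352 deserves a check against its source.

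**What to change.** Rewrite the sample size paragraph in section 4.4:

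- Print N = 2(Zα + Zβ)² · SD² / δ², with SD = 352 as the value that produced the stated number, and delete S = 3.52.
- Verify 352 against the cited study.
- Say whether 15% is a between-group difference in progression.
- Restate the power, or the detectable difference, at 22 per group for change on the scale that will be analysed, adjusted for baseline. Take the SD of change from a cited source, or from study data pooled over groups without looking at group differences. Failing both, show results over a stated range.
- If 22 per group does not give 90%, report the power that it does give rather than enrol more patients.

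The cost is one paragraph, with no added patients or procedures. The downside is that the stated power may become less favourable.
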